Exploration (IDEAL Stage 2b): A study researching the impact of adjunct TP use against a retrospective control gives a first impression of major CIED infection rates with and without TP (ClinicalTrials.gov Identifier: NCT05576194). These rates may be compared with comparative effectiveness measures from randomised controlled trials (RCTs) of other interventions used for the same purpose. The results could be used for a case number calculation for the planning of future studies. A case–control study of CIED extraction will investigate the reasons for CIED removal. Controls with similar risk factors for CIED infection undergoing CIED placement will be matched to the cases eligible for CIED hardware removal in the event of CIED infection. This is the only study with enough CIED infections to allow multivariable modelling of causation. Its results could guide the participant selection of an initial RCT in selected patients and the case number calculation of an ultimate RCT in unselected patients. 

Assessment (IDEAL Stage 3). Treatment guidelines may mention potential infection prevention with taurolidine after a first RCT of TP against the standard of care as defined in the treatment guidelines at that point in time. This may be the FederaL University of Schleswig-Holstein’s CIED Irrigation Trial (FLUSH-IT) with its comparator of no disinfection of the CIED and its components, or the Worldwide Antibiotic Stewardship in CIED Infection Prevention Trial (**WASH-IT**), which compares the intervention with adjunct TP, without preoperative intravenous antibiotic administration versus the standard of care at that point. To keep the size (and cost) of such a project reasonable, participants are selected according to their potential to benefit from the treatment, and the primary endpoint is defined to prove the direct effect. 

Long-term (IDEAL Stage 4). The ETPR begun at stage 2a will accumulate large case numbers to estimate small event rates more precisely; the plan aims to follow up on participants for years afterwards to reveal possible late effects. At the same time, results from the controlled cohort study and a matched case–control study, plus multiple interim analyses of the registry, are needed for an eventual RCT to begin. The prospective registry should therefore continue for the surveillance of established techniques (SOP from www.etpr.eu). 

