### Sample Size

The performance goals for the rate of major CIED infections vary according to country, evidence level, CIED type, and patient selection. They are expected to be higher in a revision procedure involving a complex CIED in high-risk patients than for de novo implants in otherwise healthy patients within a well-maintained setting. Additionally, the novel criteria for major CIED infection have evolved [1]. Accordingly, the published 12-month rates range from 0.7% to 4.2% (Table 3). The three-month rates are available from WRAP-IT and the Danish device registry, with values of 0.8% and 1.0% in controls, respectively [32]. For future studies researching TP use, we expect to plan for a 12-month rate of 0.5%. If its ratio to the three-month rate is 0.8/1.2, as in the WRAP-IT controls [8], then we assume a three-month rate of 0.33%.

For an approximate 95% confidence interval, to exclude a risk difference of 0.8% − 0.33% = 0.47%, when the true event rate is 0.33%, the sample size needs to exceed 572. 

For an exact 5% binomial test to have a power of 80% in detecting the difference between the hypothetical rate of 1% (0.8%) and the true rate of 0.33%, the sample size needs to be 1140 (2000).

Assuming a major CIED infection rate in the registry of 0.5% at 12 months and 0.33% at 3 months, a comparison with the performance criteria from the literature would require the sample sizes shown in Table 3.

We therefore plan to publish the ETPR results after the twelve-month follow up of 400, 900, 1420, and 2300 procedures. For the long-term evaluation, a report after the follow-up period of 36 months is planned for all procedures enrolled.

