## Figures and Tables

**Figure 1 mps-06-00086-f001:**
[figure not shown]
Enrolment and follow-up of ETPR participants; CIED denotes cardiac implantable electronic device.

**Table 1 mps-06-00086-t001:** Follow-Up Schedule.

Post-Procedure Visits	De Novo (Including Lead Only in Upgrade or Downgrade)	Box Exchange
Hospital discharge	**X**	**X**
1 month	X	
3 months	**X**	**X**
12 months	**X**	**X**
24 months	**X**	**X**
36 months	**X**	**X**

X, clinical routine; **X**, registry follow-up recorded.

**Table 2 mps-06-00086-t002:** Intercurrent events, their handling in the analysis for the first sensitivity estimand, and the rationale. The prevented bias is the bias that would have been incurred without action. The possible bias is a bias that may be incurred by the action. CI = confidence interval, MNAR = missing not at random, MAR = missing at random.

Intercurrent Event	Prevented Bias	Action	Analysis Strategy	Missingness Assumed	Possible Bias
Other or no disinfectant	Upward	No follow-up	Principle stratum	MNAR	Downward
No permanent implantation	Downward	No follow-up	Principle stratum	MNAR	Upward
Conversion to open surgery	Upward	Full follow-up	Treatment policy	--	Upward
Antibiosis for infections not related to CIED	?	Full follow-up	Treatment policy	--	?
Pocket hematoma, septic thrombophlebitis	?	Full follow-up	Treatment policy	--	?
Minor CIED infection	?	Full follow-up	Treatment policy	--	?
Box exchange	Upward	Competing risk	Hybrid	MNAR	Wide CI
System modification	Upward	Competing risk	Hybrid	MNAR	Wide CI
Other intervention touching the CIED pocket	Upward	Competing risk	Hybrid	MNAR	Wide CI
Death	Upward	Competing risk	Hybrid	MNAR	Wide CI
Lost to follow-up for another reason	Upward, narrow CI	Censoring	Treatment policy	MAR	Wide CI

**Table 3 mps-06-00086-t003:** Historic major CIED infection rates and sample sizes N needed to demonstrate superiority over such external fixed performance goals, if the true new rate is 0.5% at 12 months or 0.33% at 3 months. Sample sizes in bold are selected to issue registry reports.

Source	Follow Up (Months)	Historic CIED Infection Rate (Literature)	Hypothetical CIED Infection Rate (ETPR)	N for Approximate 95% Confidence Interval	N for Exact Test with Power 80%
WRAP-IT [8] verum	3	0.45%	0.33%		
WRAP-IT [8] verum	12	0.7%	0.50%	4778	12200
WRAP-IT [8] control	3	0.80%	0.33%	**572**	2000
WRAP-IT [8] control	12	1.2%	0.50%	**391**	**1420**
PADIT [7]	12	1.03%	0.50%	**681**	**2300**
Henrikson [33]	3	1.0%	0.33%	282	1140

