Danish registry [32]	6?	1.43%	0.50%	221	**880**
FLUSH-IT control	12	2.4%	0.50%	53	330
US insurance [9]	NR	4.2%	0.50%	14	101
Polyzos low [34]	NR	1.0%	0.33%	282	1140
Polyzos low [34]	NR	1.0%	0.50%	765	2370
Polyzos high [34]	NR	1.3%	0.33%	135	608
Polyzos high [34]	NR	1.3%	0.50%	299	1050

NR = not reported.

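### The 900-procedure report rests on a Danish registry goal whose rate and follow-up time differ between the Sample Size text and Table 3; some other Table 3 rows are mislabelled

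*Protocol article*

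**What the plan says.** The Sample Size part of Section 6 introduces the performance goals. On three-month rates it says: "The three-month rates are available from WRAP-IT and the Danish device registry, with values of 0.8% and 1.0% in controls, respectively". The citation there is [32]. On twelve-month rates it says "Accordingly, the published 12-month rates range from 0.7% to 4.2% (Table 3"). It then fixes the registry's own planning rates: "Assuming a major CIED infection rate in the registry of 0.5% at 12 months and 0.33% at 3 months". Reports are to follow twelve months of follow-up in 400, 900, 1420 and 2300 procedures.

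The caption of Table 3 says that the bold sample sizes were chosen for issuing reports. The rows that matter are:

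- Danish registry: "Danish registry [32] 6? 1.43% 0.50% 221 880", with 880 in bold.
- The only row with 1.0% at a stated three months belongs to another source: "33] 3 1.0% 0.33% 282 1140".
- A row called "FLUSH-IT control" stands in the column of historic literature rates, at 12 months and 2.4%, with no citation number.
- The US insurance row (4.2%) and the four rows from source [34] have follow-up marked NR (not reported). Each [34] rate appears twice, once against 0.33% and once against 0.50%.

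Section 2 presents FLUSH-IT under Stage 3, as a trial that may become the first randomised comparison: "Irrigation Trial (FLUSH-IT) with its comparator of no disinfection of the CIED and its components".

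**The concern.** A fixed performance goal can be interpreted only if its rate and its follow-up time are both known and the registry rate is taken at the same time. For source [32] the article gives two rates and two time points, and the question mark shows that one of the time points was still open. This row is not mere background, because its N appears to set one of the four reports.

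At stake is what the 900 report may claim. Depending on which version of the Danish goal is right, 900 procedures are either roughly enough or clearly too few. The labelling problems add to this. A reader who takes 0.7% to 4.2% as the published 12-month range, or 2.4% as a literature rate, will see goals that the table does not document as published 12-month results.

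**Working it through.** **1. The two statements on source [32].**

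| Place | Source | Follow-up | Rate |
|---|---|---|---|
| Sample Size text | Danish registry [32] | 3 months | 1.0% |
| Table 3 | Danish registry [32] | 6, with question mark | 1.43% |
| Table 3 | [33] | 3 months | 1.0% |

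**2. Reproducing the Danish row.** For the confidence-interval column, N = p1(1 − p1) × [1.96/(p0 − p1)]². With p0 = 1.43% and p1 = 0.50% this is 0.005 × 0.995 × (1.96/0.0093)² = 221.0, and the table gives 221. The same formula gives 572.0, 390.0, 680.4 and 281.5 where the table has 572, 391, 681 and 282. For the exact test with 80% power, the smallest N is 899 with a minimum-likelihood two-sided 5% test and 910 with 2.5% in the lower tail. The table gives 880. The row was therefore computed from 1.43% against 0.50%, which the caption defines as the registry's 12-month rate.

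**3. Which report depends on it.** The bold figures are 391, 572, 681, 880, 1420 and 2300. The 400 report matches 391 (WRAP-IT control, 12 months, 1.2%). The 1420 report is the same goal with the exact test. The 2300 report matches PADIT (12 months, 1.03%). All three goals are listed at 12 months and compared with 0.50%. Only 880 lies close to 900. The article does not spell out this link; it is inferred from the bold type.

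**4. Power at 900 procedures.** Let c be the largest number of infections at which the exact test rejects p0. Power is P(X ≤ c) for X ~ Binomial(900, p1).

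| Goal p0 | True p1 | Equal-tail 2.5%: c, power | Minimum-likelihood 5%: c, power |
|---|---|---|---|
| 1.43% (Table 3) | 0.50% | 5, 70% | 6, 83% |
| 1.0% at 3 months (text) | 0.33% | 3, 65% | 3, 65% |
| 1.2% at 12 months (WRAP-IT control) | 0.50% | 4, 53% | 4, 53% |

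In the first row the convention decides: six infections have a lower-tail probability of 0.0271, just above 0.025, but a minimum-likelihood p-value of 0.049. The text says only that the test is exact at 5%; Section 6 gives a two-sided 0.95 confidence level. For 1.0% against 0.33%, Table 3's own N is 1140 (1164 to 1180 on recomputation).

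**5. If 1.43% is a six-month rate.** The article gives no six-month registry rate. Assume that it lies between 0.33% and 0.50%. The N needed with 2.5% in the lower tail then runs from 611 to 910, and equal-tail power at 900 from 92% down to 70%.

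**6. If the text's 1.0% is carried to 12 months.** With the article's own ratio, 1.0% × 1.2/0.8 = 1.5%. Against 0.50%, c = 6 and power at 900 is 83% under both conventions.

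**7. The 12-month range.** The rows listed at 12 months are 0.7%, 1.03%, 1.2% and 2.4%. The 4.2% row is NR. The 2.4% row is the control of a trial that Section 2 treats as future. What remains as published with documented 12-month follow-up is 0.7% to 1.2%.

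**The case against.** The strongest reply is that the two Danish figures need not conflict. One registry can report 1.0% at three months and 1.43% later, because cumulative incidence rises, and 1.5% from the article's own ratio is close to 1.43%. That is possible, and the documents cannot exclude it. It does not explain why Table 3 gives 1.0% at three months only to a stated source other than [32], nor does it remove the question mark.

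A second reply concerns direction. If 1.43% is a six-month rate, setting a 12-month registry rate against it is conservative, since the registry has longer to accrue infections. This stands. It would be wrong to infer that the mismatch by itself makes a superiority finding at 900 invalid.

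A third reply is that the low power figures answer questions that the 900 report was not meant to answer, because Table 3 assigns 1420 to the 1.2% goal and 1140 to 1.0% against 0.33%. That is fair. The figures show only what 900 can support if the Danish goal is withdrawn or read as in the text.

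Three stronger readings are tempting and not supported:

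- That the goals in general are unmatched. Three of the four report sizes rest on matched 12-month rows. The NR and FLUSH-IT rows are not bold and size no report, and the NR entries are the authors' own disclosure.
- That the 900 report is underpowered against 1.43%. This holds with equal tails but not with the minimum-likelihood test.
- That an ineffective product would beat the 2.4% or 4.2% goals. This needs an assumed untreated rate near 1.2%. The article says that goals vary with country, device and patient selection, and that some centres treat only high-risk patients, so the untreated rate in this registry is not known.

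**Conclusion.** The point holds in a limited form. The article gives source [32] two different rates at two different times, and the row with the unresolved time is the evident basis of the 900 report. The other three report sizes, including the final 2300, are unaffected.

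The size depends on how the conflict is resolved. Power at 900 is 70% or 83% against 1.43% (by test convention), 83% if the text's 1.0% is scaled to 12 months, about 65% against 1.0% at three months, and 53% against the documented 12-month control rate of 1.2%. These figures assume true registry rates of 0.50% at 12 months and 0.33% at three months, as the article does, and a two-sided 5% exact test. Which Danish rate is right cannot be settled without the cited sources.

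Three labelling errors stand regardless: 4.2% is called a 12-month rate although its follow-up is not reported; the control rate of a possible future trial is listed as historic literature; and the [34] rates, with no reported follow-up, are tested at both horizons.

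**What to change.** - Check [32] and [33] against the sources, and make rate, follow-up time and citation agree between the Sample Size text and Table 3.
- Compare each goal with the registry rate at the same horizon. If the Danish figure proves to be a six-month rate, state the assumed six-month registry rate. Recompute the 880 and restate what the 900 report can show.
- Name the exact-test convention (equal-tail or minimum-likelihood).
- Limit superiority claims to rows with documented three- or twelve-month follow-up. Show the NR rows, and the Danish row until it is resolved, as descriptive context, and label the FLUSH-IT rate as a planning assumption.
- Correct the published 12-month range to 0.7% to 1.2%, as Table 3 now stands, unless the source check documents further 12-month rates.

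The cost is a correction to one table and a few sentences. No change to enrolment or to the final 2300 is needed. The stated power of the 900 report may become less favourable.

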## 6. Statistical Analysis

The ETPR is designed for comparisons between the intervention with TP and historical controls, with a two-sided confidence level of 0.95. The primary estimand is the rate of patients who develop a CIED infection after a CIED procedure with adjunct TP before a repeat procedure (i.e., system modification) on that CIED is performed or the patient succumbs. This rate of infection is needed to evaluate the intervention with TP during CIED placement procedures. Exact binomial statistics will be used for CIED infection rates at 3 and at 12 months, estimated as the number of procedures followed by a CIED infection relative to the number of registered procedures with at least the respective follow-up times or an event within the specified time periods. For the first sensitivity estimand, the intercurrent events (Table 2) of generator replacement, system change, revision (i.e., any procedure that touches the CIED within the follow-up period), and death are considered to be competing risks in the estimation of the cumulative incidence curve. Event times end at these events, as these events can trigger CIED infections, but sub-distribution hazards are used to calculate the cumulative incidence function. This leads to fewer upward-biased estimates than when considering these intercurrent events as censoring the event time. Censoring is restricted to failure to follow-up (i.e., death, discontinuation) and the end of observation (i.e., system modification). Other intercurrent events, such as the intravenous administration of antibiotics (e.g., in the treatment of pneumonia), will not be considered, as in the published intention-to-treat data. Their sum is expected to be independent of TP use. This decision is taken to avoid estimates that are too low for the evaluation of the intervention.

Another objective is to gather planning data for future studies. In randomised controlled trials (RCT), the primary estimand is the cause-specific hazard ratio. This translates into censoring at the occurrence of competing risks. The second sensitivity estimand of the ETPR is the rate of major CIED infections per time survived without competing risks. 

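### The exact-test sample sizes do not consistently deliver 80% power at the plan's two-sided 95% level, and no single error level tried reproduces the column

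*Protocol article*

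**What the plan says.** Section 6 of the protocol article sets the level: "The ETPR is designed for comparisons between the intervention with TP and historical controls, with a two-sided confidence level of 0.95". It also names the method: "Exact binomial statistics will be used for CIED infection rates at 3 and at 12 months".

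The Sample Size section then gives two sizes for the 3-month comparison. The claim opens "For an exact 5% binomial test to have a power of 80% in detecting the difference between the hypothetical rate of 1% (0.8", where the figure in brackets is the second goal, 0.8%. Taking 0.33% as the assumed registry rate, the section concludes that "the sample size needs to be 1140 (2000", so 1140 belongs to the 1% goal and 2000 to the 0.8% goal. It does not say whether the 5% is one-sided or two-sided.

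The alternatives for Table 3 are introduced with "Assuming a major CIED infection rate in the registry of 0.5% at 12 months and 0.33% at 3 months". The last column of the table lists sizes for an exact test with 80% power, for superiority over fixed performance goals. Bold sizes trigger registry reports. In this column they are 880 (row "Danish registry [32"], goal 1.43%), 1420 (goal 1.2%) and 2300 (goal 1.03%). Reports are planned at 400, 900, 1420 and 2300 procedures. The 400 report appears to come from the neighbouring confidence-interval column (391), which claims no power.

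**The concern.** Superiority over a fixed goal at a two-sided 95% level normally means that the upper limit of the exact 95% interval lies below the goal. That is a lower-tail test at 2.5%. If some sizes in the column were found at 2.5% and others at a looser level, the 80% label does not mean the same thing in each row.

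The stake is the stated power of the two 3-month comparisons in the text and of the interim report at 900. A reader who takes 80% at face value would put the chance of missing a true benefit at 20%, when under the equal-tailed test it is about 30% at 900 procedures. The registry is also meant to supply planning data for later trials, so its own planning figures should be reproducible.

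**Working it through.** **Inputs.** Goal rate p0, assumed registry rate p1 (0.33% at 3 months, 0.5% at 12 months) and N, all from Table 3 and the Sample Size section. Two-sided 95% level from Section 6.

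**Check that the rates are read correctly.** The confidence-interval column follows from N = 1.96² × p1(1 − p1) / (p0 − p1)². For 0.8% against 0.33%: 3.8416 × 0.0033 × 0.9967 / 0.0047² = 572, as printed. The same formula gives the printed 4778, 53 and 14. So p0 and p1 are understood as the authors used them.

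**Exact test.** For each N, let c be the largest count with P(X ≤ c | N, p0) no greater than the tail level. Power is P(X ≤ c | N, p1).

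Example, N = 1140, p0 = 1%, p1 = 0.33%:
- P(X ≤ 4 | p0) = 0.011 and P(X ≤ 5 | p0) = 0.029. At 2.5%, c = 4; at 5%, c = 5.
- Power is P(X ≤ 4 | p1) = 67.5% at 2.5%, and P(X ≤ 5 | p1) = 82.1% at 5%.

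All filled rows, plus the report at 900:

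| N | Goal vs assumed rate | Power, 2.5% lower tail | Power, one-sided 5% |
|---|---|---|---|
| 12200 | 0.7% vs 0.5% | 79.98% | 88.7% |
| 2000 | 0.8% vs 0.33% | 78.0% | 86.9% |
| 1420 | 1.2% vs 0.5% | 82.1% | 89.5% |
| 2300 | 1.03% vs 0.5% | 81.6% | 87.9% |
| 1140 (printed twice) | 1.0% vs 0.33% | 67.5% | 82.1% |
| 880 | 1.43% vs 0.5% | 72.0% | 84.4% |
| 900 (report) | 1.43% vs 0.5% | 70.3% | 83.2% |
| 330 | 2.4% vs 0.5% | 77.1% | 91.5% |
| 101 | 4.2% vs 0.5% | 60.3% | 60.3% |
| 2370 | 1.0% vs 0.5% | 78.6% | 85.6% |
| 608 | 1.3% vs 0.33% | 67.5% | 85.6% |
| 1050 | 1.3% vs 0.5% | 72.5% | 84.0% |

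The 1140 pair is counted once, which gives 11 distinct rows without the 900 line. At 2.5%, eight fall short and three deliver 80% (12200 after rounding).

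**Does a one-sided 5% test explain the column?** No. The smallest N reaching 80% would be 913, 1641, 1093 and 1765, where the plan prints 1140, 2000, 1420 and 2300. By contrast, 1420 is exactly the smallest N at 2.5%. Row 101 has c = 0 at both levels, because P(X ≤ 1 | p0) is already 0.071. It would need 131 (2.5%) or 112 (5%) to touch 80%.

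**Does any other single level?** Twelve tail levels from 0.01 to 0.10 were tried. None matched more than 6 of the 11 sizes to within 3%. Mid-p, randomised, score, Wald and arcsine versions do not reproduce the whole column either.

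**Test version.** A two-sided exact test that orders outcomes by likelihood admits c = 6 at N = 900 (lower tail 0.027), giving 83.2%. The same test gives 71.6% at 1420, and still 67.5% at 1140, 78.0% at 2000 and 72.0% at 880.

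**Saw-tooth.** Power does not rise steadily with N. Against 1.43% it is 82.5% at 910, 79.8% at 950 and 76.3% at 1000. At 2.5%, the smallest N touching 80%, and the N from which power stays there, are:
- 1.0% vs 0.33%: 1164 and 1439
- 0.8% vs 0.33%: 2132 and 2295
- 1.43% vs 0.5%: 910 and 1005

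**The case against.** **The 5% may be one-sided.** The Sample Size section does not say, and Table 3 speaks of superiority. On that reading 10 of 11 rows reach 80%, so for those rows the fault would be a mismatched error level and not too little power. This stands as a possible explanation of some rows. It does not rescue the column: it contradicts the two-sided level in Section 6, makes most sizes larger than needed, and leaves 101 at 60.3%.

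**The 70% at 900 depends on the test.** This is correct. Section 6 does not choose between an equal-tailed and a minimum-likelihood exact test, and the second gives 83.2% at 900. But it takes 1420 down to 71.6%, so neither version makes all the printed sizes right.

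**The misses are small in N.** Also fair: 1140 is 2% below 1164, 880 is 3% below 910, and 2000 misses by 2 points of power. The discreteness of the test magnifies a small gap in N. The power at the printed size is still what the label claims.

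**Stronger readings that a reader might infer.** One is that the registry as a whole is underpowered. The documents do not support that: with the equal-tailed test, 1420 and the planned total of 2300 exceed 80% against their goals, and 1140 and 2000 do not trigger reports. Another is that failing to exclude 1.43% at 900 would count against the product. The protocol sets no such rule. Section 6 bases conclusions on the latest interim or final results, so the 900 report is superseded by later ones.

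**Conclusion.** The point holds as an inconsistency in the planning figures. At the level declared in Section 6, with an equal-tailed exact test, 8 of 11 sizes miss the stated 80%, by 1.4 points (2370) to 19.7 points (101). Both sizes in the text are among them, at 67.5% and 78.0%. One planned report is affected: 900 procedures, 70.3% against 1.43%, conditional on the equal-tailed test. Row 101 is wrong under the equal-tailed, one-sided 5% and minimum-likelihood tests alike.

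This rests on the printed rates, on independent binomial outcomes, and on reading a two-sided 95% level as 2.5% in the lower tail. No planned estimate, confidence interval or total enrolment changes.

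**What to change.** - State once the sidedness and version of the exact test. An equal-tailed two-sided 5% test matches the exact 95% interval and Section 6.
- Recompute the exact-test column of Table 3 on that basis and correct the 101 row.
- Keep the planned report sizes and restate the power: about 68% (78%) for 1140 (2000) in the text, and about 70% for the 900 report against 1.43%.
- If sizes for 80% are printed instead, give those above which power stays at or above 80%: about 1439 and 2295 for the text, and about 1005 for the 1.43% goal. The saw-tooth minima 1164, 2132 and 910 should not be used. Section 6 counts only procedures with complete follow-up for the period or an event, so the analysed N cannot be fixed exactly, and a few more procedures can drop power below 80% again.

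The cost is a correction to one table and one paragraph, and a less favourable stated power for one interim report. Enrolment and the planned total of 2300 stay as they are.

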The confidence level will not be adjusted for multiple checks, as all analyses will be performed, and conclusions will be based on the latest results of the interim analyses or final results only. Times to major CIED infection or to death will be analysed using Kaplan–Meyer curves and cause-specific hazard ratios for the numbers of risk factors related to the patient, the CIED, or the procedure. ADE and complications will be analysed similarly using logistic regression.

The secondary estimand is all-cause mortality after CIED procedures using TP between procedures accessing the pocket. Intercurrent events are handled similarly (see Table S1 in the online supplement).

To facilitate causal inference in future research, the known risk factors for major CIED infection are reported. Their distribution should enable the calculation of propensity scores or more general balancing weights [31]. Such analyses would consider the randomness of historic controls instead of using historic results as performance goals.

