## 7. Discussion

Infection is a major risk and a clinically significant complication after CIED placement. Despite great efforts to reduce the risk of infection, the current epidemiological data indicate that prevalence rates vary but remain a constant problem [9,35]. Certain patient groups have a much higher risk of developing CIED infection due to procedure-, device-, or host-specific risk factors [34]. Recent publications have led to a better understanding of the true incidence of CIED infections, their prevalence, and underlying pathogens [6,8,36]. A proof of concept to address the surgical site, with the aim of preventing CIED-related infections, has led and is still leading to the broad use of various agents with [6,8,37], without, or despite existing evidence [7,38]. To further address and to better understand reactions and infections related to indwelling foreign bodies, investigations like the ETPR are needed. The undertaking of a clinical investigation of a marketed device makes the undertaking of a study easier and yields results that are, in our opinion, more applicable. The ETPR consecutively enrols all patients undergoing CIED placement, upgrades, downgrades, revision, or substitution. It was designed to evaluate and follow up on these procedures using a novel antimicrobial CIED irrigation solution: TauroPace^TM^. The value of this observation comes from short-term, medium-term, and long-term follow-up observations, as CIED infections are time-dependent problems and are not limited to the days following the CIED procedure. The prevention of CIED infection over the course of time, possibly related to the use of TP, is illustrated when one compares CIED infection rates from ETPR with the respective figures from the literature. 

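### The plan sizes its reports to show superiority over literature rates from 0.7% to 4.2% but names no goal, time point or report that decides

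*Protocol article*

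**What the plan says.** Section 6 states the purpose of the analysis: "The ETPR is designed for comparisons between the intervention with TP and historical controls, with a two-sided confidence level of 0.95". Infection rates are to be estimated by exact binomial methods at both 3 and 12 months.

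The Sample Size section notes that goals differ by country, level of evidence, device type and patient selection. It then says that "a comparison with the performance criteria from the literature would require the sample sizes shown in Table 3". The caption of Table 3 describes its entries as "sample sizes N needed to demonstrate superiority over such external fixed performance goals". The goals paired with the assumed 12-month rate of 0.5% are 0.7%, 1.0%, 1.03%, 1.2%, 1.3%, 1.43%, 2.4% and 4.2%. Further rows use the assumed 3-month rate of 0.33%.

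Reports are planned at 400, 900, 1420 and 2300 procedures. According to the caption, bold type in Table 3 marks sizes chosen for issuing reports. It does not mark a deciding goal.

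On repeated analysis, Section 6 says: "The confidence level will not be adjusted for multiple checks, as all analyses will be performed, and conclusions will be based on the latest results". The Discussion says that prevention possibly related to TP "is illustrated when one compares CIED infection rates from ETPR with the respective figures from the literature".

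**The concern.** The Introduction says the registry will evaluate whether TP can reduce major CIED infection, and Table 3 speaks of superiority. A superiority conclusion against a fixed rate needs that rate fixed in advance, together with the time point and the analysis at which it is tested. Here the goals differ by a factor of 4.2/0.7 = 6, two time points are open, and four reports draw on different goals.

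One observed rate can therefore lie clearly below some goals and not others, and the plan does not say which result counts. A goal chosen after the rate is known cannot be repaired by later analysis. At stake is whether a published claim of superiority over historical controls carries the 95% confidence that Section 6 attaches to it.

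**Working it through.** **Inputs.** Goals, assumed rates and report sizes come from Table 3 and the Sample Size section. The two-sided 95% level comes from Section 6. The infection rate these patients would have without TP is not given. It is an assumption below, and a range is shown.

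**The plan's own figures.** For the approximate interval, N = 1.96² × p1(1 − p1)/(p0 − p1)², with p1 the assumed TP rate and p0 the goal.
- p0 = 1.2%, p1 = 0.5%: 390.0 (Table 3: 391)
- p0 = 1.03%, p1 = 0.5%: 680.4 (681)
- p0 = 0.8%, p1 = 0.33%: 572.0 (572)
- p0 = 0.7%, p1 = 0.5%: 4777.8 (4778)

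For the exact test with 0.025 in the lower tail, power at a true 0.5% is 82.1% for N = 1420 against 1.2%, and 81.6% for N = 2300 against 1.03%. Both fit the stated 80%.

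**Goals behind the reports.** The 400 report corresponds to 391 (goal 1.2%), the 900 report to 880 (goal 1.43%), the 1420 report to goal 1.2% and the 2300 report to goal 1.03%. The 2.4% and 4.2% rows have no bold entry and set no report.

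**Chance of passing each goal if TP does nothing.** For goal g and size N, let c be the largest x with P(X ≤ x | N, g) ≤ 0.025. The upper exact 95% limit lies below g when X ≤ c, which has probability P(X ≤ c | N, true rate). At N = 2300:

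| Goal | c | True rate 1.2% | True rate 1.03% |
|---|---|---|---|
| 1.03% | 14 | 0.3% | 2.2% |
| 1.2% | 17 | 2.1% | 9.6% |
| 1.43% | 21 | 11.9% | 34% |
| 2.4% | 40 | 99.0% | 99.9% |
| 4.2% | 77 | about 100% | about 100% |

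The critical counts rise with the goal, so beating at least one of a set means beating its highest member. Among the goals behind the reports (1.03%, 1.2%, 1.43%), the chance of beating at least one at 2300 is 12% at a true 1.2% and 34% at a true 1.03%, against a nominal 2.5%.

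**Sensitivity to the untreated rate.** Against the whole list (highest goal 4.2%) at 2300, the chance is 99.8% at an untreated rate of 2.4%, 85% at 3.0% and about 2% at 4.2%.

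**Would adjusting the level help?** Dividing 0.025 by eight goals still leaves 93% against 2.4% and about 100% against 4.2% at a true 1.2% and N = 2300. It would not.

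**The case against.** *No rule is written that beating any one goal is enough.* This stands. A reader might infer that the plan would declare superiority almost regardless of whether TP works. The documents do not support that: Table 3 gives the size needed against each source, and the text uses those sizes to time reports. The defect is that no rule is stated, which leaves the choice open until the rate is known.

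*The near-certain figures depend on two weak rows.* This also stands. Table 3 lists the follow-up of the 4.2% row as not reported, and the 2.4% row is the control arm of a trial that the Clinical Evaluation Plan describes as future. Centres may use TP in high-risk patients only, so higher untreated rates are possible, and then the figures fall. The 12% and 34% do not use these rows, although they rest on the 1.43% row, whose follow-up is given as 6 months with a question mark.

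*Lack of multiplicity adjustment is not the fault.* Correct. The hypotheses are nested, and one exact interval is valid against every threshold at once. With a true rate of 1.2%, excluding 2.4% is a true statement. The error would lie in reading it as a TP effect.

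*Repeated reports.* A reader might also add up false claims over the four reports, about 5% for a single goal of 1.2%. That counts early claims which Section 6 lets later results replace, so it is not relied on here.

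*The registry mainly gathers planning data, and this is an article.* The planning aim is real, and the Discussion is cautious. But the comparison with historical controls and the word superiority are in the text and set the report sizes. If a fuller document already fixes the deciding comparison, stating it here is enough.

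**Conclusion.** The point holds in this form: the plan sizes its reports for superiority over a list of external goals and does not say which goal, time point or report decides. With no TP effect and a true rate of 1.2%, the chance of an apparent superiority at 2300 procedures runs from 2.1% to about 100% according to whether 1.2% or 4.2% is cited. Restricted to the goals that set reports, it is 12% at a true 1.2% and 34% at a true 1.03%.

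These figures assume exact 95% intervals, complete 12-month data on 2300 procedures and an untreated rate that the documents do not give. They show what the plan permits, not what it prescribes. The weakness is the open choice of goal. It should be closed before the first report.

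**What to change.** Add one decisive comparison to Section 6 before the first report, with its goal, time point and report. For example:

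> Superiority over historical controls will be concluded only if, at the 2300-procedure report, the upper limit of the two-sided exact 95% confidence interval for the 12-month major CIED infection rate lies below 1.03%. All other comparisons with Table 3, and those in the 400, 900 and 1420 reports, are descriptive.

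The plan already pairs 1.03% with 2300. The condition is met with at most 14 infections. The false-claim rate is 2.2% at a true 1.03%, and power is 81.6% at 0.5%. The sponsor may fix another goal, such as 1.2% (at most 17 infections, false-claim rate 2.1% at a true 1.2%, power 95.5%), with a reason why it represents these patients without TP. The sentence on basing conclusions on the latest results should then be limited to the descriptive analyses.

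State also that meeting the goal does not by itself show a TP effect, because the untreated rate in these centres is unknown. If it were 0.7%, an ineffective TP would meet the 1.03% goal 36% of the time.

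The cost is wording only: no further procedures, data or follow-up. The downside is that early reports and easy goals can no longer carry a superiority claim.
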